### Measurement Tools

For the gestational diabetes podcast, a 5-item “Yes-No-I don’t know” awareness questionnaire and a 27-item “Yes-No-I don’t know” knowledge questionnaire were developed by the researchers. For the mental health podcast, a 4-item “Yes-No-I don’t Know” awareness questionnaire and a 26-item “Yes-No-I don’t know” knowledge questionnaire were developed by the researchers. The gestational diabetes podcast has 1 additional survey question on awareness and knowledge compared to the mental health podcast, as the podcast discussion on gestational diabetes covered additional items beyond those initially prepared in the semistructured podcast guide.

The knowledge questionnaires for each of these podcasts will address 3 key themes: risk factors, symptoms, and services or treatments. Examples of the questions asked can be found in Table 1.

The only qualitative question asked at the end of each podcast is the following:

“Do you have any further comments on the podcast (duration or formatting), questions asked, or recommendations for future podcasts?”

**Table 1 table1:** Example of questions asked on knowledge and awareness.

Topic	Area being assessed	Examples of question asked before and after the podcast
Gestational diabetes	Knowledge	Is obesity or BMI a risk factor for gestational diabetes mellitus?
Gestational diabetes	Awareness	Have you heard of metformin?
Mental health	Knowledge	Is a history of mental illness in a blood relative family member a risk factors for mental illness?
Mental health	Awareness	Are you aware of risk factors for mental health problems?

### Study Population

The study will collect data from undergraduate general nursing students from 4 universities located across Ireland, South Africa, and Malawi.

### Sampling and Sample Sizes

The sample will consist of a cohort of undergraduate nursing students from University College Cork (UCC) and the University of Galway (Ireland), the University of Fort Hare (South Africa), and Mzuzu University (Malawi). These students will be recruited through invitation via the university they are attending. Entry into the study will be entirely voluntary.

The main aim is to compare the pre- and postpodcast scores on knowledge and awareness differences with a paired 2-tailed *t* test. The inputs that will be used are the expected mean (SD) of the paired differences. As this is a feasibility study, a formal sample size calculation is not required [28].

### Inclusion and Exclusion Criteria

Exclusion criteria include those who are unable to complete the web-based questionnaires due to a lack of internet connection. These surveys are solely available via Google Forms and are thus inaccessible without an internet connection. Participants will be excluded if they are not a current resident and a registered undergraduate general nursing student of Ireland, South Africa, or Malawi and do not agree to consent to the study. As this is a feasibility study, we are targeting a small cohort of individuals who are convenient to the research team. Inclusion criteria encompass those aged 18 years and older.

### Data Collection and Management

Questionnaires will be made using Google Forms, which are stored on UCC’s Microsoft OneDrive. The questionnaires will include closed-ended questions using a point scale, with points given to the tick-the-box answers of “Yes”, “No,” or “I don’t know.” These questionnaires will be distributed to UCC (Ireland), University of Galway (Ireland), University of Fort Hare (South Africa), and Mzuzu University (Malawi). Regarding the data collection, the investigators will not seek names or emails from the participants, and the data will be fully anonymized. Fully anonymized data are achievable in this study, as participants are not required to complete two different surveys. The pre- and postpodcast questions are on a single Google Form, separated only by the embedded podcast file (not 2 separate survey forms), allowing a direct comparison of survey responses without requiring participant contact details. Once the survey is submitted, the option to withdraw will no longer be available. Answers to our survey (questionnaires) will be stored on UCC-supplied Google Forms and uploaded to OneDrive. Data on knowledge and awareness will be collected from both pre- and postpodcast surveys. Information on gender, age, year of study, and the university the student is attending will also be stored, along with the consent forms. The UCC-supplied OneDrive will also be used during data collection and data analyses due to the ability to store data generated on the cloud automatically. Data will be stored for a minimum of 10 years. The data will be controlled by the UCC study members. General Data Protection Regulation will be observed at all times with all information anonymized.

Data collection tools will be structured according to the research themes outlined as follows:

#### Podcast Knowledge

Participants will be asked about their knowledge of the global health topic by assessing knowledge of symptoms, risk factors, and treatment options associated with the disease. The Google Forms will present an individual question on symptoms, risk factors, and treatments and ask respondents to indicate whether they are symptoms, risk factors, and treatment options of the condition with response options “Yes,” “No,” or “I Don't know.” For the prompted symptoms items, “No” and “I Don't Know” responses will be combined and scored 0, and “Yes” responses will be scored 1. Total scores for prompted awareness of warning signs and risk factors as well as knowledge of symptoms, risk factors, treatment options, government policies, or screening programs will be calculated by adding the recorded responses together.

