#### Podcast Awareness

To achieve this objective, terms on awareness will focus on whether participants have previously heard of terminology associated with the specific podcast and are aware of services available for that health topic or whether they have heard of the condition or disease. With regard to awareness assessment, a scoring system will be implemented. For each question item, “No,” and “I Don't Know” responses will be combined and scored 0, and “Yes” responses will be scored 1.

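### The only scoring rule given for knowledge credits every Yes and never refers to the correct answer, so any item whose right answer is No is scored backwards

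*Protocol article*

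**What the plan says.** Under Podcast Knowledge, the protocol article describes items that "ask respondents to indicate whether they are symptoms, risk factors, and treatment options of the condition", answered Yes, No or I don't know. An example in Table 1 (Measurement Tools) is "Is obesity or BMI a risk factor for gestational diabetes mellitus". The scoring rule follows: "For the prompted symptoms items, “No” and “I Don't Know” responses will be combined and scored 0, and “Yes” responses will be scored 1". The next sentence forms totals over all the themes, ending "government policies, or screening programs will be calculated by adding the recorded responses together".

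Under Podcast Awareness the same rule is stated without limit to one theme: "For each question item, “No,” and “I Don't Know” responses will be combined and scored 0, and “Yes” responses will be scored 1". Data Collection and Management also attaches points to the box ticked and does not mention correctness. No answer key appears anywhere in the article.

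The Introduction (Overview) separates the two constructs: awareness is having heard of a term, and knowledge is something deeper. Data Analysis compares knowledge before and after the podcast with a paired t test and takes a higher mean afterwards as the sign that the podcast worked.

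**The concern.** Yes = 1 suits an item that asks whether the student has heard of something. It does not in general suit an item that asks whether something is a symptom, a risk factor or a treatment, because that question has a right answer and the answer can be No. The rule as written counts Yes answers, not correct answers.

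The total feeds the main pre-post comparison, and the country and gender subgroup analyses draw on the same scores. If some items are keyed No, the mean difference is not a difference in knowledge. If none is, the score does count correct answers, but a student who simply agrees more after the podcast looks the same as one who has learned. The article makes a broader survey and the release of more podcasts depend on a positive result, so the meaning of the score matters even in a feasibility study.

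**Working it through.** The article gives no expected gain, standard deviation or sample size calculation for these questionnaires, so there is no figure to reproduce. The check is arithmetic on the scoring rule.

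**Inputs**
- K, the number of knowledge items (Measurement Tools): 27 for gestational diabetes ("a 27-item “Yes-No-I don’t know” knowledge questionnaire were developed by the researchers") and 26 for mental health ("a 26-item “Yes-No-I don’t know” knowledge questionnaire were developed by the researchers").
- Stated rule (Podcast Knowledge): score = number of Yes answers. Applying it to all themes is an inference: it is the only rule given, and the totals add every theme.
- Keyed rule, for comparison: score = number of correct answers.
- m, the number of items whose right answer is No: not given, so a range is shown.

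**Step 1. Two extreme respondents.** Under the stated rule a fully correct student scores K − m and an all-Yes student scores K. Under a key these become K and K − m.

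| m (assumed) | Fully correct, stated rule (27 / 26 items) | All-Yes, stated rule | Fully correct, keyed | All-Yes, keyed |
|---|---|---|---|---|
| 0 | 27 / 26 | 27 / 26 | 27 / 26 | 27 / 26 |
| 5 | 22 / 21 | 27 / 26 | 27 / 26 | 22 / 21 |
| 9 | 18 / 17 | 27 / 26 | 27 / 26 | 18 / 17 |
| 13 | 14 / 13 | 27 / 26 | 27 / 26 | 14 / 13 |

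**Step 2. Effect on the pre-post difference.** On Yes-keyed items the two rules agree. On a No-keyed item the stated rule counts Yes and the key counts No. Hence

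stated gain − keyed gain = sum over the m No-keyed items of [change in P(Yes) − change in P(No)].

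This is zero if m = 0. A tendency to tick Yes that is the same before and after also contributes nothing. Otherwise the sign depends on which way answers move.

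**Step 3. Illustration on 27 items. All rates are assumed.**

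(a) P(Yes) rises from 0.6 to 0.7 on every item, whatever the key. Stated gain = 27 × 0.1 = 2.7 for any m. The keyed gain is (27 − 2m) × 0.1 if the extra Yes answers on No-keyed items replace No, and (27 − m) × 0.1 if they replace I don't know.

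(b) P(correct) rises from 0.6 to 0.8 on every item. Keyed gain = 27 × 0.2 = 5.4 for any m. The stated gain is (27 − 2m) × 0.2 if the new correct No answers replace Yes, and (27 − m) × 0.2 if they replace I don't know.

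| m | (a) stated | (a) keyed | (b) keyed | (b) stated |
|---|---|---|---|---|
| 0 | 2.7 | 2.7 | 5.4 | 5.4 |
| 5 | 2.7 | 1.7 to 2.2 | 5.4 | 3.4 to 4.4 |
| 9 | 2.7 | 0.9 to 1.8 | 5.4 | 1.8 to 3.6 |
| 13 | 2.7 | 0.1 to 1.4 | 5.4 | 0.2 to 2.8 |

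For mental health with m = 9: (a) stated 26 × 0.1 = 2.6, keyed 8 × 0.1 = 0.8 to 17 × 0.1 = 1.7; (b) keyed 26 × 0.2 = 5.2, stated 8 × 0.2 = 1.6 to 17 × 0.2 = 3.4.

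In (a) the stated rule overstates the gain and in (b) it understates it.

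**Step 4. The case m = 0.** The two rules coincide. A rise of 0.1 in P(Yes) adds 2.7 points under either, whether it comes from learning or from greater readiness to agree, and no item can tell the two apart.

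**The case against.** The case on the other side has weight.

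- **No item keyed No is shown.** Both knowledge examples in Table 1, on obesity or BMI and on family history, read as keyed Yes. If all items are, the stated rule is correct-answer scoring and re-scoring changes nothing. A reader might infer that correct rejections do score 0; the documents support this only conditionally. The full questionnaires, and perhaps a key, may sit in the full protocol. What does not follow is that this is mere missing detail: the article states a rule, and that rule ignores correctness.
- **The rule names only the symptom items.** The awareness rule, by contrast, covers every item. A reader might infer that Yes = 1 is fixed for all knowledge items, but the text does not say so. If it does not extend, the scoring of risk-factor and treatment items is unstated while their responses still enter the totals.
- **Pairing removes stable yes-saying.** This stands, as Step 2 shows. A reader might infer that the bias favours the podcast; nothing in the article establishes that, and illustration (b) runs the other way. Saying Yes to a true factor just heard is learning.
- **The sizes are assumed.** This stands too. It is also tempting to compare an assumed shift with the 11.54% knowledge gain that the Introduction cites from a delirium podcast. The article does not say whether that figure is absolute or relative, and the topic differs, so the comparison carries no weight.
- **Raw responses are kept.** The merging of No with I don't know affects only the score, so nothing is lost for good.

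**Conclusion.** The concern holds in conditional form. The only stated knowledge rule credits Yes regardless of the right answer. With any No-keyed item, a correct No scores 0, a wrong Yes scores 1, and the pre-post difference is distorted in a direction that depends on how answers shift. With none, the score is valid as a count of correct answers but cannot distinguish knowledge from increased agreement.

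The size cannot be fixed from the article, because the number of No-keyed items and the response rates are not given. The tables in the working show what could happen under assumed values; they are not estimates for this study. The conclusion also assumes that the rule extends from the symptom items to the other themes. Keyed scoring is never worse than the stated rule: it corrects every No-keyed item and leaves Yes-keyed items unchanged.

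**What to change.** 1. Replace the knowledge rule with: every knowledge item (symptoms, risk factors, treatments or services) scores 1 if the response matches a pre-specified answer key, and 0 if it is incorrect or I don't know. Write the key before the responses are analysed.
2. Apply it to responses already stored as well as to those still to come. Keep Yes = 1 for awareness items only.
3. Report how many of the 27 and 26 items are keyed No.
4. Tabulate pre-to-post moves among correct, incorrect and I don't know. The keyed score still merges the last two, and the table shows whether a gain came from corrected beliefs or from filled gaps.
5. If no item is keyed No, state as a limitation that gains may partly reflect agreement.

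The cost is a written key, a spreadsheet change and one extra table; no new contact with participants is needed. Adding false items now is not part of this fix. Data collection is under way, the podcasts are already recorded, and approvals from three ethics committees are in place, so a changed questionnaire would split respondents across two instruments and would not be a minor step.

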#### Podcast Awareness

To achieve this objective, terms on awareness will focus on whether participants have previously heard of terminology associated with the specific podcast and are aware of services available for that health topic or whether they have heard of the condition or disease. With regard to awareness assessment, a scoring system will be implemented. For each question item, “No,” and “I Don't Know” responses will be combined and scored 0, and “Yes” responses will be scored 1.

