Knowledge and awareness have often been used synonymously, but in this study, a distinction between these 2 interchangeable words is set. Knowledge has been described as “the fact or condition of knowing something with familiarity gained through experience or association,” the “acquaintance with or understanding of a science, art, or technique,” and “the range of one's information or understanding” [11]. Awareness has been described as “knowledge and understanding that something is happening or exists” [12]. In our study, awareness will be defined as having heard of a term or topic, while knowledge will be defined as a deeper understanding of the area.

The podcast topics are as follows:

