### Data Analysis

Microsoft Excel and Google Forms will be used to capture raw quantitative data and to execute the descriptive statistics in the form of percentages and frequencies. Descriptive statistics, including percentages, means, and standard deviations will be calculated for participants’ survey responses. For the pre- and posttest analysis, a paired 2-tailed *t* test analysis for the questions that assess medical knowledge will be performed. The means of both the pre and posttests will be calculated. The pretest will act as the control, and therefore, *P* values will be determined to identify if the results are statistically significant. This analysis will enable the observation of whether the podcasts were an effective intervention tool by examining a higher posttest mean score. Significance will be defined as *P*<.05.

This is an international feasibility study, and it would be of great interest to analyze participants’ country of residence in conjunction with the level of knowledge and awareness gained from the podcast to give us an insight into which country would benefit most from this form of audio learning. To conduct this, we will perform a subgroup analysis in SPSS. Furthermore, men and women have been shown to learn differently, with women preferentially being auditory learners [29]. Therefore, a subgroup analysis on gender will be carried out on SPSS. This research will help to clarify whether podcasting is a useful educational resource that is of benefit to both sexes as an alternative source of learning [30].

For this study, we only have 1 open-ended question, which is “Do you have any further comments on the podcast (duration or formatting), questions asked, or recommendations for future podcasts?” We will conduct a thematic analysis of the responses to open-ended questions [31]. To analyze and describe the comments, a coding frame will be developed. If responses contain 2 or more different statements, these statements or sentences will be coded separately or line by line.

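### A pre/post rise on the have-you-heard-of awareness items cannot be credited to the podcast, because the pretest itself names the term; the article also gives two scopes for the paired t test

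*Protocol article*

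**What the plan says.** The Overview in the Introduction separates the two outcomes: "awareness will be defined as having heard of a term or topic, while knowledge will be defined as a deeper understanding of the area". In the Podcast Awareness section this is carried into the items: "terms on awareness will focus on whether participants have previously heard of terminology associated with the specific podcast". It then adds a second kind of content, namely whether they "are aware of services available for that health topic or whether they have heard of the condition or disease". Yes scores 1; No and I don't know score 0.

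Measurement Tools gives 5 awareness items for gestational diabetes and 4 for mental health. The column of example items in Table 1 is headed "Examples of question asked before and after the podcast". The awareness example for gestational diabetes is "Have you heard of metformin". The one for mental health asks whether the student is aware of risk factors for mental health problems.

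Data Collection and Management places both sets of questions on a single form with only the embedded podcast between them. Data Analysis makes the pretest the control and reads effectiveness from a higher posttest mean, at P<.05.

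On the scope of the test, Sampling and Sample Sizes states the main aim as to "compare the pre- and postpodcast scores on knowledge and awareness differences with a paired 2-tailed" t test. Data Analysis says that a paired t "test analysis for the questions that assess medical knowledge will be performed"; awareness returns there only for the comparison of gains between countries.

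**The concern.** Under the article's own definition, measuring this kind of awareness creates it. A student who had never met the word metformin has met it once the pretest item is read, whether or not the podcast is then played. On such an item a truthful answer can stay level or rise, but it cannot fall. There is no group that answers twice without the podcast, so the rise has no comparator.

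The awareness result is put to use. The third research question asks whether podcasting is effective for awareness. Type of Study and Setting will judge effectiveness on knowledge and awareness, and a broader survey depends on positive results. The Conclusions describe a positive result as an increase in both. Data Analysis will compare awareness gained between countries. To the extent that heard-of items drive the change, a country that starts lower has more room to gain whatever the podcast does.

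The two statements of the test's scope add to the difficulty: a reader cannot tell whether the change in awareness score is to be tested at all.

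**Working it through.** **No figure to reproduce.** The article states no sample size, power or effect size. The 2395 in the Abstract is the total number of students at the four universities (850 + 450 + 719 + 376 = 2395), not an expected number of respondents.

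**The mechanism, step by step.**
1. Awareness means having heard of a term or topic (Overview).
2. The example item names the term (Table 1).
3. The item is asked before and after the podcast (Table 1 heading), on one form (Data Collection and Management).
4. The pretest is the only control (Data Analysis).
5. So at posttest every respondent has met the term through the pretest item, and Yes is truthful regardless of the podcast.

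**Which items this covers.** Steps 2 and 5 hold for items of the form have-you-heard-of-X. They do not hold for items on services or on being aware of risk factors: being asked about risk factors does not make one aware of them. The article shows one awareness example per topic, out of 5 and 4, so the number of each kind is unknown.

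**Illustration of size.** Assumptions that are not in the article: all k items are of the heard-of kind (an upper end); each has baseline Yes rate p; every answer other than Yes becomes Yes at posttest. Let q = 1 − p.

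- Mean gain = k·q
- SD of the change if items are independent = √(k·q·(1 − q))
- SD of the change if items are fully correlated = k·√(q·(1 − q))
- n = smallest number giving 80% power in a two-sided paired t test at 0.05 (noncentral t)

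For k = 5:

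| Baseline Yes | Mean gain | SD, independent | n | SD, fully correlated | n |
|---|---|---|---|---|---|
| 80% | 5 × 0.20 = 1.00 | 0.894 | 9 | 2.00 | 34 |
| 90% | 5 × 0.10 = 0.50 | 0.671 | 17 | 1.50 | 73 |
| 95% | 5 × 0.05 = 0.25 | 0.487 | 32 | 1.09 | 152 |

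If only half of the other answers become Yes (independent items), q is halved and n becomes 17, 32 and 64. For k = 4 with independent items, n is 10, 20 and 40 if all change, and 20, 40 and 79 if half change.

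**Near the ceiling.** With independent items, a 98% baseline and 100 respondents, the simulated chance of significance lies between 0.54 and 0.99 over the 4- and 5-item scores and the two shares changing. A ceiling can hide the artefact; it does not make a change interpretable.

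**Scope of the test.** Sampling and Sample Sizes: paired t test on knowledge and awareness. Data Analysis: paired t test on the questions that assess medical knowledge. The two sections describe the same main analysis with different outcome sets.

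**The case against.** Several stronger readings are tempting, and the article does not support them.

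- **That the whole awareness score rises by construction.** Podcast Awareness includes services, and the mental health example in Table 1 is not a heard-of item. Those answers may be pushed upward, as self-report often is, but they are not forced.
- **That the follow-on criterion would be met automatically.** The criterion is joint with knowledge, so an awareness gain alone does not satisfy it.
- **That the country ranking on gain must reverse the baseline ranking.** This needs every posttest answer in every country to be Yes.
- **That the podcast's own naming of a term is an artefact.** Under the article's definition, hearing a term in the podcast is the intended effect. Only the pretest exposure confounds it.
- **That a handful of respondents guarantees P<.05.** With independent items, 6 respondents at 80% baseline and 10 at 90% give only about 60% and 56% power. Correlation between items raises the numbers needed.

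The word previously in Podcast Awareness could also mean before today. Then there is no built-in gain, but a truthful answer cannot change, so the item could show no podcast effect either. Neither reading helps with the third research question.

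On the scope of the test, Data Analysis does not say that only knowledge is tested, and awareness stays in the descriptive statistics and the country comparison. In a condensed article this may be an omission. It still leaves two statements to reconcile.

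Calling the study a feasibility study does not remove the point, since the article itself draws effectiveness conclusions from the change. Strengths and Limitations names nonresponse and selection bias, but not this.

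**Conclusion.** The point holds for heard-of items. A pre/post rise on them cannot be told apart from having read the question, so it is not evidence that the podcast worked. If all items were of this kind and all other answers became Yes, the artefact alone would be 0.25 to 1.0 points on the 5-item score at baselines of 95% down to 80%. It would be detectable with 80% power from about 9 to 32 respondents (independent items) or 34 to 152 (fully correlated). These figures rest on assumed baselines and an assumed item mix. The real baseline is not stated and may be close to the ceiling in nursing students. The reasoning about the items does not depend on those assumptions. The difference in test scope between Sampling and Sample Sizes and Data Analysis is a separate, smaller matter that needs reconciling.

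**What to change.** All changes are to wording and can be made before the analysis planned for March 2024:

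1. Report heard-of items at baseline only, as prior awareness by university and year of study.
2. Do not use their pre/post change for the third research question, for the country comparison in Data Analysis, or for the positive-results criterion in Type of Study and Setting and in the Conclusions. Any awareness total compared before and after should leave these items out.
3. Make Sampling and Sample Sizes and Data Analysis state the same scope for the paired t test.
4. Add to Strengths and Limitations that the pretest names the terms and that no group answers twice without the podcast.

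Do not reword items now. Collection is under way, and a changed form would produce two versions of the instrument whose awareness scores could not be pooled.

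The cost is a few sentences of text, and the loss of a headline awareness gain on these items.
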